### Randomization and allocation

2.10

After screening, the patients will be randomly divided into 2 groups at a 1:1 ratio. Randomization will be performed using random numbers generated by SPSS version 21.0 (IBM Corp., Armonk, NY, USA). The patients will be randomly divided into a treatment group (n = 36) and control group (n = 36), and the group assignment will be concealed from the researchers by a senior data manager who will not be involved in the study. The group assignments will be sealed in opaque envelopes and be opened by the researchers following acquisition of informed consent and completion of baseline testing.

### Blinding

2.11

All of the investigators, physicians, nurses, assessors, analysts, and participants will be blinded to the group assignments until the end of the trial, after all statistical analyses are finished. The patients will not be blinded. If any clinically significant adverse event potentially related to the treatment occurs after the first treatment administration, the study physician will re-evaluate the participant and the principle investigator will decide whether the non-blinded procedure is necessary. If non-blinding is required, the allocation information will be provided.

### Data collection and monitoring

2.12

This is a 24-week clinical trial in which the participants will undergo the research intervention for 4 weeks with a 24-week follow-up. The primary outcome measures will be assessed at 5 time points (at baseline and at weeks 2, 4, 12, and 24), the secondary outcome measures will be assessed at 2 time points (at baseline and at week 24), and safety will be assessed at 6 time points (at baseline and at weeks 1, 2, 4, 12, and 24). All results will be independently documented by 2 investigators using EpiData version 3.1 (EpiData Association, Odense, Denmark), and differences will be resolved through discussion with a third investigator. The Longhua Hospital Affiliated to Shanghai University of Traditional Chinese Medicine will be responsible for monitoring and quality control.

### Statistical analyses

2.13

Trained statisticians will use the intentionality approach for validity assessment and safety analysis. The final outcome observation method will be applied to deal with missing values. All statistical analyses will be performed using SPSS version 22.0 (IBM Corp.). Before randomization, the patients baseline characteristics will be collected as descriptive statistics, including sex, age, body mass index, duration of symptoms, and degree of LDH. The data analysis of the primary outcome will be based on the per-protocol population as a supportive analysis. The mean, standard deviation, median, quartiles, and interquartile ranges will be calculated for continuous variables, and the frequency will be calculated for categorical variables. Continuous variables with a normal distribution will be calculated by the independent-samples Student *t* test and presented as mean with standard deviation; otherwise, the data will be analyzed using non-parametric tests and expressed as median with range.

Categorical variables will be expressed as number (%) and analyzed by the χ^2^ test or Fisher exact test. Repeated-measures analysis of variance will be used to analyze the changes in the VAS score, PPT, and ODI score at different time points (baseline and weeks 1, 2, 4, 12, and 24). An independent-samples *t* test will be used to analyze the changes in lumbar lordosis, lumbar vertebral angle, tilt angle of the first thoracic vertebra line, PI, PT, SS, and LM at baseline and 24 weeks. A *P* value of <.05 will be defined as statistically significant, and two-sided 90% confidence intervals will be calculated. Missing data will be input with the last observed response carried forward for all measures using the “last-value-carried-forward” principle.

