### Safety assessment

2.8

The project director will supervise the data collection process to assure the safety of the participants. At each visit, the participants will be required to stay in the hospital for 30 minutes after the treatment and will be asked about any adverse effects that may indicate acute adverse reactions during the study period (e.g., lower limb paralysis or cauda equina syndrome). All adverse effects will be recorded at each visit during the treatment period.

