### Sample size calculation

2.9

We estimated the sample size based on the main outcome indicators, and we conducted a randomized trial of Shi-style lumbar spine manipulation combined with Daoyin therapy versus lumbar traction from March to September 2018, with 10 participants in each group. The outcome parameter was the rate of improvement in the NDI (neck disability index) score from baseline to the end of the 8-week treatment. The results showed that the rate of improvement after Shi-based lumbar spine manipulation combined with Daoyin therapy was 92.0%, while that after lumbar traction was 86.6% (*P* = .893) (α = 0.05, test efficiency 1 − β = 0.8, and equivalent standard δ = 0.2).

Because our study protocol will involve the use of a non-inferiority test, according to the number of cases in the clinical non-inferiority and equivalent tests and the equivalent standard,^[17]^ and using counting data (rates) as the outcome indicators, the following formula was used to estimate the number of patients required for this study:$$n=2\times {\left({\text{U}}_{\alpha }+{\text{U}}_{\beta }\right)}^{2}\times \text{p}(1-\text{p})/\delta^{2}$$

2 × (U_α_+ U_β_)^2^was calculated as 12.365, and N was 29.537 after substituting the above figures, and the sample size of each group was about 30 cases; according to the loss rate of 20%, the sample size of each group was 36 cases, and the ratio of treatment group and control group was 1:1, a total of 72 cases.

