### Monitoring

2.14

Two supervisors will be sent to the study site twice a month to guarantee the quality of the whole trial. These supervisors will audit the clinical trial, including adverse events, inclusion and exclusion criteria, participant compliance with the clinical trial process, and completion of the case report forms. Standard operating procedures will be invariably followed. Drop-outs, withdrawals, and any noncompliance will be recorded in detail by the inspectors throughout the treatment and follow-up periods. This process will be independent from the investigators and the sponsors.

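### The only safety analysis stated groups patients by assigned arm, although the protocol's harms are reactions after treatment; define a treated, as-received safety set

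*Protocol article*

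**What the plan says.** Statistical analyses (2.13) sets one principle for efficacy and harm together: "Trained statisticians will use the intentionality approach for validity assessment and safety analysis". The only other population it names is confined to efficacy: "The data analysis of the primary outcome will be based on the per-protocol population as a supportive analysis". The article defines no set of treated patients for safety.

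Safety assessment (2.8) keeps patients in hospital for half an hour after treatment, when they are "asked about any adverse effects that may indicate acute adverse reactions during the study period (e.g., lower limb paralysis or cauda equina syndrome"). Blinding (2.11) likewise provides for re-evaluating a patient after a possibly treatment-related event that follows the first treatment.

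Randomization and allocation (2.10) states: "The patients will be randomly divided into a treatment group (n = 36) and control group (n = 36"). The envelopes will "be opened by the researchers following acquisition of informed consent and completion of baseline testing", which is before any treatment. Monitoring (2.14) adds: "Drop-outs, withdrawals, and any noncompliance will be recorded in detail by the inspectors throughout the treatment and follow-up periods".

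**The concern.** The rule for counting harms does not match the kind of harm being looked for. Sections 2.8 and 2.11 tie an adverse event to a physical treatment that has been given. The assigned-arm rule ties it to the envelope. The two agree only when every patient starts and stays on the assigned treatment.

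- **Never started.** A patient who declines after the envelope is opened has no post-treatment observation, yet stays in the denominator as event-free. That lowers the arm's rate.
- **Other arm's treatment received.** An event after manipulation in a patient assigned to traction is counted under traction, and the reverse.

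The named events (lower limb paralysis, cauda equina syndrome) are serious and the arms are small, so a single event can carry the safety statement. Section 2.9 describes the comparison as non-inferiority. An analysis that can mute a difference in harm is a poor choice as the only one stated.

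**Working it through.** **1. The plan's own figure.** The document gives no adverse-event, switch or never-start rate, so the only figure to reproduce is the arm size (2.9). With p = (0.920 + 0.866)/2 = 0.893 and δ = 0.2, n = 12.365 × 0.893 × 0.107 / 0.04 = 29.54. This rounds to 30, and 30 × 1.2 = 36 per arm. It reproduces. The point uses only the 36.

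**2. Granularity.** One event is 1/36 = 2.8% of an arm.

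**3. Never-starters.** Rate by assignment = rate among treated × (1 − share never starting). The 6 events and the numbers never starting are assumptions:

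| Never start, of 36 | By assignment | Among treated |
|---|---|---|
| 0 | 6/36 = 16.7% | 6/36 = 16.7% |
| 2 | 6/36 = 16.7% | 6/34 = 17.6% |
| 4 | 6/36 = 16.7% | 6/32 = 18.8% |
| 7 | 6/36 = 16.7% | 6/29 = 20.7% |

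Seven is close to the planned loss ("according to the loss rate of 20%, the sample size of each group was 36 cases"; 7/36 = 19.4%). That figure covers loss of any kind, so it is at most a rough upper guide for non-starting.

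**4. Effect on the contrast.** Assume true event rates of a = 20% after manipulation and b = 5% after traction. Let s_M and s_T be the shares never starting in each arm, and c the share of traction patients who receive manipulation instead. By assignment:

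- manipulation arm = a(1 − s_M)
- traction arm = b(1 − s_T − c) + a·c

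| s_M | s_T | c | Manipulation | Traction | Difference (points) | Ratio |
|---|---|---|---|---|---|---|
| 0 | 0 | 0 | 20.0% | 5.0% | 15.0 | 4.0 |
| 10% | 10% | 0 | 18.0% | 4.5% | 13.5 | 4.0 |
| 0 | 0 | 10% | 20.0% | 6.5% | 13.5 | 3.1 |
| 10% | 10% | 10% | 18.0% | 6.0% | 12.0 | 3.0 |
| 20% | 20% | 20% | 16.0% | 7.0% | 9.0 | 2.3 |
| 0 | 20% | 0 | 20.0% | 4.0% | 16.0 | 5.0 |

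Switching alone narrows both measures. Equal non-starting narrows the difference and leaves the ratio unchanged. Non-starting in the traction arm only widens both, so the overall direction is not fixed.

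**The case against.** **The reading is inferred.** The word intentionality is not defined, and the article does not say how untreated patients or events after non-assigned treatment are counted. A full protocol or SAP might. This stands as a caution. But the article does not stay silent on safety: it names a principle for it and limits the alternative population to the primary outcome. A later safety set would depart from the published rule.

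**Switching is not described.** No crossover is provided for, and both treatments are scheduled by arm. A reader might infer that traction patients will seek manipulation, because all patients enter willing to have it (2.1.1), "The patients will not be blinded" (although the sentence before says participants are), and treatment stops at week 4. The documents do not support that as an expectation. Willingness is not switching, and the gap after week 4 applies only to traction, since Daoyin continues for 6 months (2.3). Manipulation obtained outside the trial need not be the Shi-style technique, so charging its harms to the experimental arm could itself be a misattribution.

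**The direction is not always the unsafe one.** A reader might infer that assignment-based grouping always makes the arms look alike. The last row of the second table shows otherwise.

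**The shifts are small against the noise.** With 3 events, 3/36 = 8.3% has an exact 95% interval of 1.8% to 22.5%, and 3/29 = 10.3% one of 2.2% to 27.4%. One misplaced event (0/36 against 1/36) has Fisher P = 1.0, so no formal comparison is reversed. This stands. What changes is the description of which treatment preceded a serious event.

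**Serious cases are reviewed individually.** Sections 2.11 and 2.14 provide for re-evaluation and audit. That protects the patient, but does not decide the reported table.

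**Conclusion.** The point holds as a mismatch between a stated rule and the protocol's own safety question. It rests on reading the undefined term as intention-to-treat. Its effect is zero if everyone starts and stays on the assigned treatment. Otherwise it distorts an arm's rate or an event's attribution by an amount that cannot be derived from the document; every event, switch and never-start rate above is an assumption. In those illustrations an arm's rate moves by at most 4 points (16.7% against 20.7%, with 7 of 36 untreated). The document does not support a claim that switching is to be expected, that harms will be understated, or that a safety conclusion would be reversed. The change is justified because it is conventional and nearly free.

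**What to change.** In section 2.13:

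- Keep intention-to-treat for efficacy, and name it as such.
- Make the main safety analysis all patients who received at least one study session, grouped by the study treatment actually received.
- List separately any event that follows a switch or a non-study treatment, using the noncompliance records already required by section 2.14.
- Keep the randomised-arm safety table as a secondary display.

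A case report form question at existing visits about other back treatment would help to identify such events, since section 2.3 asks patients to record only medication. It is optional.

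The cost is a short addition to the text. Sample size, treatment and the efficacy analysis do not change. The downside is that as-received groups are not strictly randomised, which is why the randomised-arm table stays alongside.

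### The sample size rests on a non-inferiority test, but per-protocol is only supportive to an intention-to-treat analysis with last value carried forward, and no rule covers disagreement between the two

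*Protocol article*

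**What the plan says.** Section 2.9 (Sample size calculation) gives the design basis: "Because our study protocol will involve the use of a non-inferiority test". Its parameters are "α = 0.05, test efficiency 1 − β = 0.8, and equivalent standard δ = 0.2", applied to an improvement rate on the neck disability index from a pilot with 10 patients per group. It allows for 20% loss and arrives at 36 per arm, 72 in total.

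Section 2.13 (Statistical analyses) assigns the analysis sets. Efficacy and safety follow an approach whose name is oddly translated but which I read as intention-to-treat. On the other set it says: "The data analysis of the primary outcome will be based on the per-protocol population as a supportive analysis". On missing values: "Missing data will be input with the last observed response carried forward for all measures". No other missing-data method is named. Significance is P < .05, with two-sided 90% confidence intervals. The section does not say what follows if the two sets disagree.

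Section 2.12 puts the primary outcomes at baseline and weeks 2, 4, 12 and 24. Manipulation and traction end at week 4. Daoyin continues for 6 months in the treatment arm only (section 2.3).

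**The concern.** Making intention-to-treat primary and per-protocol supportive is the usual order for a superiority test, where diluting the contrast works against the sponsor's claim. In a non-inferiority test, dilution can work for the claim. Patients who leave early or do not adhere stay in the comparison. If their carried-forward values are alike in both arms, a true deficit looks smaller than it is.

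The protocol itself expects one patient in five to be lost, so this is not a remote case. At stake is whether a non-inferiority conclusion would reflect the treatments or the dropout. These are choices that the protocol states, not details left open for an analysis plan.

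**Working it through.** **1. Reproduce the plan's figure.** Inputs from section 2.9: rates 0.920 and 0.866, so p = (0.920 + 0.866)/2 = 0.893; margin 0.2; α = 0.05; power 0.80.

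- 2 × (1.645 + 0.842)² = 12.365
- n = 12.365 × 0.893 × 0.107 / 0.2² = 29.537, so 30 per arm
- 30 × 1.2 = 36 per arm, 72 in total

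This matches the text: "was calculated as 12.365, and N was 29.537 after substituting the above figures". The multiplier shows that α was used one-sided; the two-sided value would give n = 37.5. A two-sided 90% interval corresponds to the same one-sided 5%.

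**2. False-claim rate without dilution.** A false claim occurs when the lower 90% bound lies above −0.20 although the true difference d is exactly −0.20. By normal approximation its probability is

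Φ((d + 0.20)/SE − 1.645), with SE = √[pT(1 − pT)/36 + pC(1 − pC)/36].

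With pC = 0.893 and pT = 0.693, SE = 0.0925 and the rate is Φ(−1.645) = 5.0%. Exact binomial enumeration of the Wald interval gives 5.8% (control rate 0.866) to 6.1% (control rate 0.893).

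**3. Balanced loss with no between-arm difference among dropouts.** The documents do not give the carried-forward response rate q, so I let it run from 0 to 0.8, the same in both arms. Example with 20% loss and q = 0.5:

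- pT = 0.8 × 0.693 + 0.2 × 0.5 = 0.6544
- pC = 0.8 × 0.893 + 0.2 × 0.5 = 0.8144
- d = −0.16, SE = 0.1024
- rate = Φ(0.04/0.1024 − 1.645) = 10.5%

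Over both control rates and all values of q:

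| Loss in each arm | Expected d | Approximation | Exact |
|---|---|---|---|
| 0% | −0.20 | 5.0% | 5.8-6.1% |
| 10% | −0.18 | 7.2-7.6% | 7.4-9.1% |
| 20% | −0.16 | 9.8-11.2% | 10.0-13.0% |

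**4. Late dropouts.** A patient lost after week 4 carries forward a post-treatment value, which may contain the deficit. If half of the 20% loss keeps the full deficit (an assumption), d = −(0.8 + 0.1) × 0.20 = −0.18. The rate is then much the same as in the 10% row.

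**5. Unequal loss, dropouts carried forward as failures** (assumed splits, treatment/control):

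- 30%/10%: 0.3-0.4%
- 25%/15%: 2.2-2.4%
- 15%/25%: 27-28%
- 10%/30%: 51-55%

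**6. Power of the per-protocol set.** I assume that this set is the completers, 36 × 0.8 ≈ 29 per arm, with both rates at 0.893. SE = √(2 × 0.893 × 0.107/29) = 0.0812. Power = Φ(0.20/0.0812 − 1.645) = Φ(0.819) ≈ 79%.

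**The case against.** Four points can fairly be made against the concern.

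- **The direction is not fixed.** A reader might infer that intention-to-treat with carried-forward values always favours non-inferiority. The documents do not support that. Only the treatment arm has a 6-month exercise programme, so heavier loss there is plausible. If those patients carry forward poor values, the analysis becomes conservative (step 5). This stands, and the point has to be put as a possibility. It does not rescue the plan, because the error rate would still depend on an unknown dropout split.
- **The size is easily overstated.** Using the planning variance, SE = √(2 × 0.893 × 0.107/36) = 0.0729, would give 13.7% at 20% loss and 8.5% at 10%. That places both arms at 0.893 while assuming that they differ by 20 points, so the variance is too small. Nor do all dropouts carry near-baseline values: only those lost before week 2 carry baseline itself. Both corrections stand.
- **Section 2.13 never applies the margin to any analysis set.** It lists t tests, χ² or Fisher tests and repeated-measures analysis of variance, with no non-inferiority comparison. The abstract and discussion speak of efficacy and effectiveness. That non-inferiority will be judged on the intention-to-treat set is therefore an inference from the roles given to the two sets. This stands, and it is why the fix has two branches.
- **Per-protocol analysis can also be biased,** the more so with unblinded patients. This too stands, and it argues for requiring agreement of both sets instead of exchanging one for the other.

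**Conclusion.** The concern holds in conditional form. The sample size is built for non-inferiority, while the ranking of the analysis sets suits a difference test and has no rule for disagreement. With a true deficit at the margin, 36 per arm, and a balanced 20% loss that contributes no difference between arms, the false-claim rate roughly doubles, from about 5-6% to about 10-13%. At 10% loss it is about 7-9%.

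These figures rest on assumptions that are not in the documents: the carried-forward response rates, the split of loss by arm, and a binary outcome analysed with a Wald interval. The 20% scenario is near the upper case for balanced loss. The figures also use the rate and margin of section 2.9; the listed primary outcomes (VAS, pressure pain threshold, ODI) have no stated margin. Intention-to-treat is not wrong in itself, and a per-protocol analysis is already planned. The weakness is its subordinate role, with carrying forward as the only missing-data method.

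**What to change.** Choose the aim and align sections 2.9 and 2.13.

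- **If non-inferiority is kept:** state in 2.13 that it is claimed only if the lower bound of the two-sided 90% confidence interval meets the margin in both the intention-to-treat and the per-protocol analyses. Name the primary outcome and define the margin on its scale, with the sign set so that a lower bound marks the unfavourable side. The present 0.2 belongs to a neck disability index improvement rate, which is not among the listed outcomes.
- **If the aim is a difference test:** remove the non-inferiority statement from 2.9, restate the basis of the sample size there, and keep per-protocol as supportive.

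Cost: both analyses are already planned, so the agreement rule is one sentence. Defining a margin, or a new sample-size basis, takes more work. Success becomes somewhat harder: about 79% power for the per-protocol set alone at about 29 completers per arm, and slightly less when both sets must agree. The rule does not replace carrying forward; it only keeps a claim from resting on that analysis alone.

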## Method/design

2

The purpose of this prospective randomized controlled clinical trial is to investigate whether Shi-style spine manipulation combined with Daoyin therapy can lead to improvements in middle-aged and elderly patients with LDH. The study will be conducted in the Department of Orthopaedics, Longhua Hospital, Shanghai University of Traditional Chinese Medicine. The principal investigator will be responsible for the entire project, including organization of the steering committee meetings. An independent steering committee will be responsible for participant safety, meetings, participant recruitment, and quality control. The coordination center will be responsible for communicating protocol modifications and providing materials. The trial will involve 4 weeks of treatment and 6 months of follow-up. After randomization, the patients will receive one course of treatment within 4 weeks. The results will be evaluated at baseline and at weeks 2, 4, 12, and 24.

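### The one analysis tied by name to VAS, PPT and ODI names no between-arm effect and no deciding contrast, and is not linked to the comparison with traction or the non-inferiority test

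*Protocol article*

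**What the plan says.** Statistical analyses (2.13) contains four relevant statements.

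- For the primary outcomes: "Repeated-measures analysis of variance will be used to analyze the changes in the VAS score, PPT, and ODI score at different time points".
- For continuous variables in general: "Continuous variables with a normal distribution will be calculated by the independent-samples Student *t* test and presented as mean with standard deviation", with non-parametric tests otherwise. No outcome or week is attached.
- For the imaging outcomes: "An independent-samples *t* test will be used to analyze the changes in lumbar lordosis, lumbar vertebral angle", continuing through the remaining imaging measures, at baseline and 24 weeks.
- For all analyses: "A *P* value of <.05 will be defined as statistically significant, and two-sided 90% confidence intervals will be calculated".

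Elsewhere, Method/design (2) gives the purpose as "to investigate whether Shi-style spine manipulation combined with Daoyin therapy can lead to improvements in middle-aged and elderly patients with LDH", with no comparator in the sentence. Sample size calculation (2.9) says "Because our study protocol will involve the use of a non-inferiority test" and sizes the trial on an improvement rate with a margin of 0.2. The Discussion (3) states a comparison of effectiveness with mechanical pelvic traction. On timing, Data collection and monitoring (2.12) says "The primary outcome measures will be assessed at 5 time points (at baseline and at weeks 2, 4, 12, and 24"); the ANOVA sentence in 2.13 adds a week 1.

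**The concern.** A two-arm repeated-measures ANOVA tests three effects: time, arm, and arm by time. Only the last two concern the randomised comparison. The effect that the primary sentence describes, change across visits, is closest to the first. The null hypothesis of the time effect is that the pooled mean does not change over the visits. Natural course, regression to the mean, analgesic use and two active treatments can each make that null false when the arms do not differ at all.

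The purpose in section 2 could also be met by improvement from baseline alone. The Abstract promises convincing evidence of efficacy. With the deciding effect left open, a significant time effect on VAS, PPT or ODI could be offered as that evidence, although randomisation does not protect it.

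**Working it through.** **1. The plan's own figure.** It shows that the stated design is a between-arm one. Inputs from 2.9: pilot rates 92.0% and 86.6%, α = 0.05, power 0.80, δ = 0.2.

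- p = (0.920 + 0.866)/2 = 0.893
- 2 × (z₀.₉₅ + z₀.₈₀)² = 12.365
- n = 12.365 × 0.893 × 0.107 / 0.2² = 29.537, so 30 per arm

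Both printed values (12.365 and 29.537) reproduce. The calculation compares two rates between arms against a margin at one-sided 0.05, which matches the two-sided 90% interval in 2.13. Section 2.13 does not carry this comparison or its margin over to any outcome.

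**2. How many P values are open.** For each primary outcome the ANOVA can give 3 effects (time, arm, arm by time). If the generic t test also applies at each of the 4 post-baseline visits, that makes 3 + 4 = 7 P values per outcome. Nothing in 2.13 says which one decides.

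**3. How often the pooled time effect is significant when the arms do not differ.** The article gives no SD or within-patient correlation for VAS, PPT or ODI, so these are assumed:

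- 5 visits (baseline and weeks 2, 4, 12, 24);
- equal correlation ρ of 0.3, 0.5 or 0.7 between visits;
- the same improvement d (in SD units) in both arms, half reached by week 2 and all by week 4;
- n = 36 per arm (randomised) or 30 (before the allowance for loss);
- 3,000 simulated trials per setting, tested at P < .05.

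| Common improvement d | Time effect, n = 30 (ρ = 0.3 / 0.5 / 0.7) | Time effect, n = 36 (ρ = 0.3 / 0.5 / 0.7) |
|---|---|---|
| 0 | 0.051 / 0.044 / 0.041 | 0.042 / 0.051 / 0.053 |
| 0.2 SD | 0.217 / 0.308 / 0.483 | 0.262 / 0.355 / 0.575 |
| 0.3 SD | 0.479 / 0.634 / 0.872 | 0.566 / 0.727 / 0.933 |
| 0.5 SD | 0.928 / 0.988 / 1.000 | 0.972 / 0.996 / 1.000 |
| 0.8 SD or more | 1.000 throughout | 1.000 throughout |

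In the same trials the arm effect, the arm-by-time effect and a t test on week-24 change were significant in about 4–6% in every setting (0.041 to 0.062).

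**4. Check by formula.** The mean profile is d × (0, 0.5, 1, 1, 1), with average 0.7d. The squared deviations sum to (0.49 + 0.04 + 3 × 0.09) d² = 0.80 d². The noncentrality of the time F test is λ = 2n × 0.80 d² / (1 − ρ). For n = 36, d = 0.5, ρ = 0.5: λ = 72 × 0.80 × 0.25 / 0.5 = 28.8. With 4 and 280 degrees of freedom this gives power 0.995, against 0.996 simulated. For n = 36, d = 0.2, ρ = 0.3: λ = 72 × 0.80 × 0.04 / 0.7 = 3.29, power 0.262, against 0.262 simulated.

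**5. The proposed analysis.** A separate simulation (36 per arm, 4,000 trials, d = 0.5, ρ = 0.4 / 0.6 / 0.8) gave 0.986 / 0.999 / 1.000 for time, and 0.047 / 0.046 / 0.053 for a baseline-adjusted arm comparison of the mean post-baseline score.

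**The case against.** The strongest reply is that the sentence is shorthand. A repeated-measures ANOVA in a two-arm trial ordinarily has arm as a between-patient factor. The generic t test in 2.13 is a two-group test, and nothing excludes VAS, PPT and ODI from it. The imaging sentence is built in much the same way and does not mention arm either. Sections 2.9 and 3 show that a comparison with traction is intended. P < .05 is a general significance level, not a rule attached to the time effect. A journal article may also leave the model term to a fuller document.

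Much of this stands. A reader might infer that the ANOVA is the only primary analysis, that its time effect is the decision rule, and that the trial therefore has a false-positive rate near 100%. The documents support none of these three steps.

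Two further limits also stand. The pilot rates concern a neck disability score over 8 weeks, so they do not show how far VAS, PPT or ODI will move. And under the non-inferiority design of 2.9, equal improvement in both arms is a case where the trial is meant to succeed. The simulation therefore shows that the time effect is uninformative about treatment; it does not show a wrong non-inferiority conclusion.

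The point survives all the same. The article does not simply leave the method out: it names one for the primary outcomes and describes its target as change over visits. If the generic t test also applies, the primary outcomes have two analyses with no ranking. Neither is linked to the non-inferiority comparison for which the trial was sized.

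**Conclusion.** The concern holds in a limited form. Section 2.13 ties one analysis by name to VAS, PPT and ODI, describes it as change over time, and fixes neither a between-arm effect nor a deciding contrast. It does not carry through the comparison with traction or the non-inferiority test. One of the P values left open, the pooled time effect, is significant in about 93–100% of trials with no arm difference once both arms improve by 0.5 SD, and in practically all at 0.8 SD or more. At 0.2 SD the range is 22–58%, so near-certainty depends on the size of the common improvement. Between-arm tests stay at about 4–6%.

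These figures rest on assumed SDs, correlations and time course, and they matter only if the time effect is used as evidence of efficacy. The plan allows that use but does not prescribe it.

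**What to change.** In 2.13:

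- State that the conclusion for VAS, PPT and ODI rests on the baseline-adjusted between-arm difference, from ANCOVA or from a repeated-measures model with baseline as covariate. Name the week or average that decides, and report the difference with its confidence interval.
- State the hypothesis against which that difference is judged, after reconciling it with 2.9. If non-inferiority is kept, the interval must be compared with a margin. The stated 0.2 applies to an improvement rate, so it does not carry over directly to a difference in mean scores. A non-significant arm or arm-by-time test does not show non-inferiority. If superiority is meant, 2.9 needs to say so.
- State that time main effects and within-arm changes are descriptive and do not support an efficacy claim.

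In section 2, word the aim as improvement compared with traction.

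The cost is a few sentences, with no new data or visits. Reconciling the hypothesis may mean revisiting the basis of the sample size. The downside for the sponsor is that improvement within an arm can no longer be presented as the primary result.
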